### Study settings

The study is a parallel, double-blind, randomized controlled trial. Participants for this trial will be recruited from the communities of Shahrasti and Chandpur, Bangladesh, where arsenic levels in tube well water frequently exceed the national standard of 50 ppb. Families in these rural areas typically have their own tube well in the yard from which they collect their drinking and cooking water. Entire families will be recruited.

### Inclusion criteria

The inclusion criteria are as follows:Families who are exposed to arsenic levels ≥100 ppb in their drinking water will be included in the trial.All family members aged 14 and above will be enrolled if they agree.

### Exclusion criteria

The exclusion criteria are as follows:Children under the age of 14 will not be included in the trial, although they will also eat the high-selenium or control lentils like the rest of the family.Families whose tube well water has arsenic levels <100 ppb will be excluded from the trial.If any family member(s) appears unhealthy, anemic for example, the family will not be recruited.

#### Justification for eligibility criteria

The national standard for arsenic in drinking water is 50 ppb. To increase the possibility of detecting clinical differences between the two treatments, we chose families with wells having arsenic levels above the national standard and ≥100 ppb. Moreover, after testing all the tube wells of potential participants, we identified only 10 out of 118 wells that had arsenic levels between 50 and 100 ppb. This resulted in a small sample size for this subgroup, which may not produce interpretable results and could weaken the statistical power of the whole trial.

We planned to include children of ages 10–17 in the trial, as they are a vulnerable group and actively developing, especially those from ages 10 to 14. The observation of changes in nutritional status in these children due to lentil consumption would be especially valuable in our opinion. However, the Ethics Review Committee at icddr,b stipulated that children under the age of 14 be excluded from the study. Nevertheless, all family members of study participants, including young children, will eat the high-selenium or control lentils.

### Consent

Informed consent will be obtained from all adults, which includes their children in the trial, and assent forms are collected from every recruited child between 14–18 years of age (see Additional files 2 and 3). All forms have been translated into Bangla, and the recruiters will explain the trial procedures in detail and answer any questions the participants may have.

### Interventions and compliance

Families will be randomly assigned to one of two interventions:High-selenium lentilsLow-selenium lentils

For a period of 6 months, each participant will be required to eat 65 g lentils each day. The group that receives the high-selenium lentils will therefore consume at least the US-RDA of 55 μg selenium per day. Apart from lentil supply, the other food consumed daily will not be controlled, so study participants who are in the low-selenium lentil group will also receive selenium from other food sources as usual, but this is expected to be similar between groups. The female family head will measure 65 g lentils per family member each day (a measuring cup will be provided) and will prepare foods, such as dal (lentil soup) and lentil patties, that are generally eaten by the family members over the day. The field staff will visit families twice a week in the first month of the intervention to promote and record compliance in lentil consumption. To ensure and confirm compliance, the lentil supply will be distributed weekly, and study participants will complete a lentil consumption questionnaire on a weekly basis for the duration of the trial.

We performed a 1-week pilot trial with four families to determine likelihood of compliance. The four families received the adequate amount of lentils (purchased from the local market) for 1 week, and consumption was monitored. All families did eat the required amount of lentils. The female family head used different recipes to incorporate the lentils into the daily meals.

### Safety considerations

We do not expect any adverse effects from lentil consumption regardless of the treatment groups since both types of lentils are already traded and consumed worldwide. The group that will consume the high-selenium lentils will receive the US-RDA of 55 μg of selenium per day, plus the average of 23 μg selenium in the regular Bangladeshi diet acquired through other components, primarily fish and meat [13]. The current tolerable upper intake levels of selenium for humans are 280 μg/day (9–13 years) and 400 μg/day (ages 14+) according to the Dietary Supplement Fact Sheet from the National Institutes of Health, USA [23]. Supplementation of selenium at 200 μg/day in studies of up to 13 years duration — in addition to other dietary selenium intake — lowers the risk of cancers, enhances cell-mediated immune function, decreases progression of chronic infectious diseases, inflammation and autoimmune diseases, and presents no evidence of toxicity [24–27]. Hence, even if study participants consumed double the amount of lentils a day, their selenium intake would be well below toxic levels and would likely be beneficial to their health.

An independent DSMB at icddr,b has been formed which will conduct periodic meetings and report the occurrence of adverse or seriously adverse events, if any. In this highly unlikely event, unblinding would be permissible.

### Sample size

We determined the sample size for this trial with an online power and sample size calculator (www.powerandsamplesize.com), based on a one-sided effect for arsenic concentration in hair.

Based on a previous intervention trial [28], in which arsenic-exposed participants received selenium-enriched yeast (100–200 μg/day, an amount two to four times higher than our dietary treatments), we calculated the sample size from their data generated after a 9-month intervention. Using the mean arsenic levels in hair of the control and selenium-treatment groups, Mean_A_ = 2.01 μg/g (±1.4) and Mean_B_ = 1.23 (±0.73), respectively, and a type I error of 0.05 and a power of 0.80, we calculated a minimum participant number of 26 per treatment group. This sample size underestimates our needed sample size due to substantial differences from our planned trial. Considering the up to fourfold lower selenium treatment in our trial, we felt it was prudent to quadruple the number (=100) and then double it to accommodate our larger age range, shorter duration, and loss to follow-up, arriving at the final participant number of 200.

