## Methods/design

This trial protocol has been approved by the University of Calgary’s Conjoint Health Research Ethics Board (Ethics ID: REB13-1211-Mod3), the University of Saskatchewan’s Biomedical Research Ethics Board (Bio-No. 14-212), plus the Research Review Committee, the Ethics Review Committee, and the Data and Safety Monitoring Board (DSMB) of the International Centre for Diarrhoeal Disease Research, Bangladesh (Icddr,b) (Protocol No. PR-14013). Any changes to the trial protocol are communicated to the relevant parties and ethics boards. The trial will be reported according to SPIRIT (Standard Protocol Items: Recommendations for Intervention Trials) 2013 [21] (see Additional file 1). A summary of the trial according to the WHO Trial Registration Minimal Data Set is provided in Table 1 [22].

**Table 1 Tab1:** WHO Trial Registration Minimal Data Set according to Moja et al*.* [22]

Data	Information
Trial identification number	ClinicalTrials.gov NCT02429921
Trial registration date	April 21, 2015
Secondary IDs	REB13-1211 (CHREB, University of Calgary), PR-14013 (ERC, icddr,b)
Funding sources	Global Institute for Food Security (GIFS); Grand Challenges Canada - Stars in Global Health Round 5
Primary sponsor	[name], Faculty of Vet. Med, University of Calgary, Canada
Secondary sponsor	RR, icddr,b, Dhaka, Bangladesh
Responsible contact person	RR, icddr,b; [contact]
Research contact person	[name], Faculty of Vet. Med., University of Calgary; [contact]
Brief title of the study	High-selenium Lentils Versus Arsenic Toxicity
Official title of the study	Mitigating arsenic toxicity in Bangladeshi people by supplementing their diets with high selenium lentils
Country of recruitment	Bangladesh
Health problem studied	Chronic arsenic poisoning
Intervention	High-selenium lentils, control: low-selenium lentils
Key inclusion and exclusion criteria	Inclusion criteria: families with >100 ppb As in their well water; ages eligible for study: 14–75
	Exclusion criteria: As content of well water ≤100 ppb; ill health detected during initial recruitment health check
Study type	Double blind, parallel, block-randomized, controlled intervention trial
Trial start date	September 28, 2015
Target sample size	200 per treatment group (400 in total)
Recruitment status	Active
Primary outcome	Arsenic body burden: We will determine if high-Se lentil consumption will decrease the body burden of As by measurement of As excretion in urine and feces and deposition in hair

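### Quadrupling the sample size for an up to fourfold lower selenium dose offsets only a halved effect; if effect is proportional to dose, the fourfold end needs about 406 per group before other allowances

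*Protocol article*

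**What the plan says.** The Sample size section works from one comparison, "based on a one-sided effect for arsenic concentration in hair". The inputs come from an earlier 9-month trial of selenium-enriched yeast: "Mean_A_ = 2.01 μg/g (±1.4) and Mean_B_ = 1.23 (±0.73), respectively", with "a type I error of 0.05 and a power of 0.80". From these, "we calculated a minimum participant number of 26 per treatment group".

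The section says that 26 is too few for the present trial, because the earlier trial gave "100–200 μg/day, an amount two to four times higher than our dietary treatments". It then inflates in two steps. The first is for dose: "Considering the up to fourfold lower selenium treatment in our trial, we felt it was prudent to quadruple the number (=100"). The second is for other differences: "then double it to accommodate our larger age range, shorter duration, and loss to follow-up, arriving at the final participant number of 200".

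Table 1 carries the result as "200 per treatment group (400 in total"). No power and no target difference are given for 200 per group, and no relation between selenium dose and hair arsenic is stated.

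**The concern.** The first inflation step pairs a fourfold lower dose with a fourfold larger sample. That treats sample size as linear in the effect. Under the formula that yields 26, it depends on the square: halving the difference requires four times as many participants, and quartering it requires sixteen times as many. The factor of 4 is therefore the right correction for a halved effect, but it is justified by a possible fourfold reduction. The later doubling is assigned to other purposes and is not available to close the gap.

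Hair arsenic is part of the primary outcome and the only basis for the sample size. Because 26 is inflated on the ground that it is too small, a reader will take 200 per group as preserving 80% power at the lower dose. If the true effect lies near the fourfold end, a non-significant result would be quite likely even with a real benefit, and it could be read as lack of efficacy.

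**Working it through.** **Inputs.** From Sample size: means 2.01 and 1.23 μg/g, so the difference is 0.78; SDs 1.4 and 0.73, so the sum of variances is 1.96 + 0.5329 = 2.4929; one-sided 5%, 80% power; dose ratio two to four. From Table 1 and Randomization and blinding: 200 per group. Assumed here: effect proportional to dose, SDs unchanged.

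**1. Reproduce the base figure.** n = (1.645 + 0.842)² × 2.4929 / 0.78² = 25.33, rounded up to 26. This matches. (Two-sided, the same inputs give 32.2, so 33.)

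**2. Scale for a smaller effect.** With difference 0.78/f, n = 25.33 × f².
- f = 2 (0.39 μg/g): 101.3, so 102 per group
- f = 3 (0.26 μg/g): 228 per group
- f = 4 (0.195 μg/g): 25.33 × 16 = 405.3, so 406 per group

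The quadrupled figure of 100 (4 × 26 is in fact 104) thus corresponds to f = 2. At f = 4, 100 per group has 34% power.

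**3. What 200 per group delivers if the whole doubling is spent on the smaller effect.** SE = √(2.4929/200) = 0.1116. Power = Φ(difference/SE − critical value), with critical value 1.645 one-sided or 1.960 two-sided.

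| Dilution | Difference (μg/g) | Difference/SE | One-sided | Two-sided |
|---|---|---|---|---|
| 2 | 0.39 | 3.49 | 97% | 94% |
| 3 | 0.26 | 2.33 | 75% | 64% |
| 4 | 0.195 | 1.75 | 54% | 42% |

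One-sided, 80% power is kept up to f = √(200/25.33) = 2.8.

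**4. Cross-check of the dose ratio.** From Interventions and compliance and Lentil production and analysis: 65 g/day × (0.854 − 0.029) mg/kg = 53.6 μg/day between groups. The earlier 100–200 μg/day is 1.86 to 3.73 times that. At 3.73-fold the need is about 353 per group, and one-sided power at 200 is 59%.

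**5. Difference detectable with 80% power.** Difference = (critical value + 0.842) × SE. Design effect 2 and 10% loss (180 per group) are illustrative assumptions; neither stands in the article. SD 1.4 in both groups is also an assumption, made because 0.73 comes from a group that had the full effect.

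| Setting | SE | One-sided | Two-sided |
|---|---|---|---|
| Stated SDs, no clustering or loss | 0.1116 | 0.28 | 0.31 |
| Stated SDs, design effect 2, 10% loss: √(2.4929 × 2/180) | 0.1664 | 0.41 | 0.47 |
| SD 1.4 in both, design effect 2, 10% loss: √(3.92 × 2/180) | 0.2087 | 0.52 | 0.58 |

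In the last setting, power at the fourfold end is Φ(0.195/0.2087 − 1.645) = 24% one-sided and Φ(0.195/0.2087 − 1.960) = 15% two-sided. At the twofold end it is Φ(0.39/0.2087 − 1.645) = 59% and Φ(0.39/0.2087 − 1.960) = 46%.

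**The case against.** A reader might infer that the article claims 80% power for 200 per group and that the claim is false. The text does not go that far. The 0.80 is attached to 26; for 200 it is implied, because the multipliers serve to make up for the shortfall of 26.

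A reader might also infer that the trial is simply underpowered. That does not follow. Fourfold is the upper end of a two- to fourfold range. At twofold, 200 per group has 97% power. At the middle of the earlier dose range (150 μg/day against 53.6, a ratio of 2.8) it has about 80%, although that ignores clustering and spends the whole doubling on the effect. Proportionality is this review's assumption, and the article presents the factor of 4 as a prudent judgement, not a derivation. All of this stands and limits the conclusion. It does not rescue the step itself: the only reason offered for the factor of 4 is the fourfold dose reduction, and 4 is not the factor that such a reduction implies under the article's own formula if effect follows dose.

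Two further points are fair. The one-sided basis is stated openly, and silence on sidedness in a condensed analysis section is not a fault. And the figures assume an unadjusted comparison of final values. Hair is also sampled at baseline, and adjustment for it could raise power: at the fourfold end to about 64% one-sided, at an assumed correlation of 0.5 with the stated SDs and no clustering. The Data analysis section does not commit to that adjustment.

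**Conclusion.** The scaling step is wrong as written. The 26 per group reproduces, but multiplying by 4 covers a halved effect and not the fourfold reduction used to justify it. If effect is proportional to dose, the fourfold end needs about 406 per group before any allowance for age range, duration or attrition, and 200 per group gives 54% power one-sided or 42% two-sided with the stated SDs and no clustering or loss. The implied 80% holds, one-sided and under those favourable settings, up to about 2.8-fold dilution.

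The arithmetic of the base figure and of the inverse-square rule is firm. The size of the shortfall depends on proportionality and on where in the two- to fourfold range the true dilution lies; the lower figures also depend on the assumed design effect, loss and SD. The documents support a finding that the justification does not establish the implied power across its own dose range. They do not support a finding that 200 per group is inadequate throughout that range.

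**What to change.** Withdraw the quadruple-then-double argument in Sample size and state instead what 200 per group delivers:

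- The hair-arsenic difference detectable with 80% power, naming the sidedness and using the same sidedness in the analysis. With the stated SDs and no clustering or loss this is 0.28 μg/g one-sided or 0.31 two-sided. The sponsor should replace the illustrative design effect, loss and SD used above with values it can justify.
- Power at the twofold and fourfold ends under the same settings as the detectable difference, with proportionality named as an assumption. A one-sided power should not be printed beside a two-sided detectable difference.

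The cost is a rewritten paragraph and a less favourable stated power. No participants are added, and no trial procedure changes.

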### Randomization and blinding

This trial will be double-blinded. High- and low-selenium lentils have been packed in color-coded bags (green and white), and neither the study participants nor the study investigators know of the lentil type.

Related families commonly live in the same Bari (group of homes on one plot of land) in rural Bangladesh, with families, defined as members taking meals from the same cooking pot, living in individual homes or households (HHs) in the Bari. All family members in an HH will receive the same lentil type. However, within each Bari individual HHs may receive different lentil types. Once families are recruited, they will be assigned to treatment group A or B (deficient or high-selenium lentil groups) using a computer-generated block randomization method, and one group will be randomly assigned to receive selenium-rich lentils. The sample size is 200 individuals per group. Typically a family consists of four to eight members. Thus, if there are six members per HH, there will be approximately 34 HH per group. For the block randomization we may consider blocks of variable length, e.g., four or six HHs per block; thus, in each block there will be four or six HHs. Equal numbers of HHs are distributed in the two groups, and either group may receive the selenium-rich lentils. All HHs will receive their supply of lentils weekly. Sequential numbers will be allocated to the participants, e.g., 010101, 010102 (Bari 01, HH 01, family member 01, 02, 03…), etc.

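### Bari and household are coded in every participant ID, but the stated regression uses neither, so variation shared within a Bari stays in the error of the lentil comparison (a modest, conditional loss of precision)

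*Protocol article*

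**What the plan says.** Under Randomization and blinding, the protocol article describes how people live: "Related families commonly live in the same Bari (group of homes on one plot of land) in rural Bangladesh". The household is the randomised unit and all its members get one lentil type, but "However, within each Bari individual HHs may receive different lentil types". Blocks of four or six households are suggested and are not tied to the Bari. The participant number is built from Bari, household and family member, so both grouping levels are on record. "The sample size is 200 individuals per group", and the section expects about 34 households per group at six members each. The Abstract gives about 80 families in all.

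Data analysis sets out Spearman correlations and then multiple linear regression stratified by sex. Covariates enter as confounders if they correlate at p < 0.15 and change the estimate by at least 5%. Neither Bari nor household is mentioned. The Sample size section has no clustering term either.

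On exposure, Study settings says: "Families in these rural areas typically have their own tube well in the yard".

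**The concern.** Households on one plot are often kin and live over the same local groundwater, so their arsenic levels may be alike. Because lentil type can differ within a Bari, part of the comparison is already made between neighbours. A model that knows the Bari can use that contrast; one that does not leaves the shared variation in its residual.

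The confounder rule will not bring the Bari in by itself. It screens variables by correlation and change in estimate, whereas the Bari is a nominal design label with no meaningful correlation to test.

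Only some 68 to 80 households carry the comparison, so avoidable household-level variance is worth removing if it exists. At stake is the width of the interval for hair and urinary arsenic. The validity of the randomised comparison is not in question here.

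**Working it through.** **1. The plan's own figure.** The calculation is "based on a one-sided effect for arsenic concentration in hair", with "Mean_A_ = 2.01 μg/g (±1.4) and Mean_B_ = 1.23 (±0.73), respectively".
- Difference: 2.01 − 1.23 = 0.78.
- SD: √((1.4² + 0.73²)/2) = 1.116.
- n per group: 2 × (1.645 + 0.842)² × 1.116² / 0.78² = 25.3, so 26.

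This agrees with "a type I error of 0.05 and a power of 0.80, we calculated a minimum participant number of 26 per treatment group". The number is then quadrupled, and the last step is to "double it to accommodate our larger age range, shorter duration, and loss to follow-up, arriving at the final participant number of 200". No step refers to household or Bari.

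**2. Assumptions (none is in the document).**
- 72 households, between 2 × 34 = 68 and 80.
- 6 members per household, the article's own example.
- Household-level ICC (Bari and household together) of 0.1 to 0.2.
- Bari share of that household-level variance: 40%.
- Enrolled households per Bari: k = 2, 3 or 4.

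**3. Bari share of the variance of a household mean.** With total variance 1, a household mean has variance ICC + (1 − ICC)/6, and the Bari part is 0.4 × ICC.
- ICC 0.1: 0.04 / (0.10 + 0.15) = 0.04/0.25, so p = 0.16.
- ICC 0.2: 0.08 / (0.20 + 0.133) = 0.08/0.333, so p = 0.24.
- No person-level variance: p = 0.40.

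**4. Gain from using the Bari.** If households are allocated without regard to Bari, the information relative to an analysis that ignores it is approximately

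I = [(k − 1)/k] / (1 − p) + [1/k] / (1 + (k − 1)p),

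and the variance falls by 1 − 1/I. For k = 2 this reduces to p². I checked it by computing the exact variance over 400 allocations in blocks of four (ordinary least squares without Bari against generalised least squares with Bari). The exact values, in brackets, are slightly lower.

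| k | p = 0.16 | p = 0.24 | p = 0.40 |
|---|---|---|---|
| 2 | 2.6% (2.5%) | 5.8% (5.6%) | 16% (15.6%) |
| 3 | 4.4% (4.3%) | 9.3% (8.9%) | 23% (22%) |
| 4 | 5.8% (5.6%) | 11.7% (11.2%) | 27% (26%) |

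A variance cut of 2.5 to 11.2% narrows the interval by 1 − √0.975 = 1.3% to 1 − √0.888 = 5.8%. It equals 1/0.975 = 1.03 to 1/0.888 = 1.13 times as many households.

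**5. Half the households alone in their Bari.** Information becomes 0.5 + 0.5 × I. With the rest in twos at p = 0.16, I = 1.026 and the cut is 1.3%. With the rest in threes at p = 0.24, I = 1.102 and the cut is 4.9% (4.6% exact). With the rest in fours it would be about 6%. If every household is alone in its Bari, it is zero.

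**6. Households randomised in Bari order.** The blocks then balance the Baris in part, so the true variance is lower, but an analysis without Bari does not credit this. In the extreme case, four households per Bari coincide with blocks of four and the true variance is about (1 − p) of the reported one. A household-mean interval would then be too wide by a factor of 1/√0.84 = 1.09 to 1/√0.76 = 1.15. The model term adds no true precision in that case; it only corrects the standard error.

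**7. The household level, for scale.** The design effect is 1 + 5 × ICC, or 1.5 to 2.0. Treating individuals as independent would raise a nominal two-sided 5% test to about 11 to 17%: 2 × [1 − Φ(1.96/√1.5)] = 0.11 and 2 × [1 − Φ(1.96/√2)] = 0.166.

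**The case against.** The strongest objection is that this rests on what a condensed article leaves out. A random intercept is ordinary content for a full analysis plan, the covariate list is open-ended, and Data analysis does not spell out the lentil-group comparison for the primary outcome. That limits the weight of the point but does not remove it. The section states a concrete method and a concrete rule for what enters the model, and neither brings in a design factor.

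Second, separate yard wells suggest exposure specific to the household, not one Bari source, and the entry threshold for well arsenic truncates its variation. This stands: it weakens the shared-water argument and makes a small Bari share plausible. Shared kinship and local groundwater remain possible reasons for likeness.

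Third, everything that sets the size is assumed. This also stands.

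A reader might infer three stronger claims:
- **A gain of 4 to 48%.** That range appears with Bari shares of 20 to 60%, 2 to 4 households in every Bari and negligible person-level variance. Nothing in the article supports the last two conditions.
- **A gain of 17 to 60%.** Those figures need a much larger Bari share of total variance (0.05 to 0.30, with a further 0.10 for household) and an allocation balanced within each Bari. The article does not describe such an allocation and none is proposed here.
- **Bias or excess false positives from ignoring the Bari.** Allocation can vary within a Bari, so omitting it costs precision and, if anything, widens the interval. The excess in step 7 of the working comes from the household level.

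**Conclusion.** The point holds as a modest, conditional gain in precision. The article creates within-Bari contrasts and records the Bari, but its stated regression does not use it. Under the assumptions listed, the variance of the arm difference would fall by about 2.5 to 11% with 2 to 4 enrolled households per Bari. It would fall by about 1 to 5% if half the households are alone and the rest are in twos or threes, and not at all if every household is alone. If randomisation follows Bari order, a household-level interval that ignores Bari is also somewhat too wide on this account.

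The improvement is worth making because the variable is already recorded, but it is not free: the extra variance component has to be estimated. The household term in the same model matters more, since the household is the randomised unit; adding the Bari alone would not deal with that.

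**What to change.** State that the lentil-group comparisons of hair and urinary arsenic use a linear mixed model with lentil group as a fixed effect and a random intercept for household nested in a random intercept for Bari, both taken from the participant ID. Say in advance that the Bari term is dropped, and the household term kept, if the Bari variance is estimated at zero or the subset is too small to support it, as may happen with the roughly 40 participants who give stool samples.

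The allocation and data collection stay as they are. The change adds two model terms to the stated regression, of which the Bari is one. Its small downside is a variance component that may be poorly estimated if most Baris supply a single household. It would also help to report the number of enrolled households per Bari and the estimated variance shares, so that readers can see how much the term contributed.

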**Methods/design:**

A total of 400 participants (about 80 families) will be divided into two groups via computer-generated block randomization. Eligibility criteria are age (≥14) years) and arsenic concentration in the household tube well (≥100 ppb).

In this double-blind study, one group will eat high-selenium lentils grown in western Canada; the other will consume low-selenium lentils grown in Idaho, USA. Each participant will consume 65 g of lentils each day for 6 months. At the onset, midterm, and end of the trial, blood, urine and stool, plus hair (day 1 and at 6 months only) samples will be collected and a health examination conducted including assessment of acute lung inflammation, body mass and height, and blood pressure. The major outcome will be arsenic excretion in urine and feces, as well as arsenic deposition in hair and morbidity outcomes as assessed by a biweekly questionnaire. Secondary outcomes include antioxidant status, lipid profile, lung inflammation status, and blood pressure.

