### Data analysis

Data are stored in a password-protected database at icddr,b, through a platform that allows sharing of data between project investigators (PIs) at icddr,b and the University of Calgary. Statistical analyses will be done using the statistical software SPSS for Windows PASW version 20. Normality and homogeneity of variances will be determined. Data not normally distributed will be transformed as necessary. Initially Spearman’s correlation analyses will evaluate univariate association between arsenic exposure (urinary and hair arsenic) and outcome variables (oxidative stress, antioxidant status, lung inflammatory status, and genetic variables). Covariates (e.g., demographic and socioeconomic variables, morbidity, daily diet, and BMI of participants) will be evaluated for significant association with exposure and outcomes. Missing data are excluded from that specific analysis. Significantly correlated variables will be further analyzed in multiple linear regression models controlling for potential confounding variables stratified by sex. Potential confounders will be identified based on correlations (*p* < 0.15) with the exposure (toxic metal) and outcomes and will be included in the final models when they change the effect estimate for metal exposure on the outcome by 5 % or more.

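### Households are randomised, but neither the sample size nor any named analysis method takes account of household clustering

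*Protocol article*

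**What the plan says.** Under Interventions and compliance, the unit of allocation is the family: "Families will be randomly assigned to one of two interventions". Randomization and blinding defines a family by its shared cooking pot, forms blocks of four or six households, and says that "Equal numbers of HHs are distributed in the two groups" and that "All family members in an HH will receive the same lentil type". Study settings adds that families typically have their own tube well for drinking and cooking water.

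The size of the trial is set in individuals: "The sample size is 200 individuals per group". The Sample size section takes hair arsenic means and SDs from an earlier selenium-yeast trial, one-sided, with type I error 0.05 and power 0.80, and reports that "we calculated a minimum participant number of 26 per treatment group". That number is multiplied by four for the lower selenium dose, then by two for age range, shorter duration and loss to follow-up.

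Under Data analysis, "Spearman’s correlation analyses will evaluate univariate association" between urinary or hair arsenic and the outcome variables. Variables that correlate go on to multiple linear regression, stratified by sex. No household term is mentioned.

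Household numbers appear twice. Randomization and blinding says that, with six members each, "there will be approximately 34 HH per group". The Abstract says "A total of 400 participants (about 80 families) will be divided into two groups".

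**The concern.** This is a cluster-randomised design, although the article never calls it one. Members of a household share the allocated lentils, the cooking and, as a rule, the well whose arsenic level made them eligible. Hair arsenic, the endpoint used for sizing, depends on that shared exposure, so correlation within households is to be expected.

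Two things follow if the correlation is ignored. First, 200 people in 34 to 40 households carry less information about the lentil effect than 200 independent people. Second, an arm comparison that treats individuals as independent has standard errors that are too small and rejects a true null hypothesis too often. A larger sample can make up for the first problem but not for the second. The Discussion section plans policy advice on lentil imports from the results, so a false positive would have consequences.

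**Working it through.** **1. Reproduce the stated figure.** Inputs from the Sample size section: means 2.01 and 1.23 μg/g (difference 0.78), SDs 1.4 and 0.73, one-sided 0.05, power 0.80.

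n = (1.4² + 0.73²)(1.645 + 0.842)² / 0.78² = 2.4929 × 6.185 / 0.6084 = 25.3, rounded up to 26 per group.

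This matches. The two-sided version gives 33, so the printed figure is the one-sided formula for independent individuals.

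**2. Follow the inflation.** 26 × 4 = 104, written as 100; 100 × 2 = 200. None of the listed reasons is clustering. Household size enters the article only to convert people into a count of households.

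**3. Cluster size.** 200/6 = 33.3, hence about 34 households per group (68 in all). 400/80 = 5 per household, hence about 40 per group. So m = 5 to 6 on the article's own figures. Only members aged 14 and over enrol, so the enrolled m may be smaller.

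**4. Design effect.** The ICC is an assumption; the article gives none. DE = 1 + (m − 1) × ICC, and effective n = 200/DE. For an unadjusted comparison of individuals, the actual two-sided error of a nominal 5% test is 2 × [1 − Φ(1.96/√DE)].

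| Assumed ICC | DE (m = 5 to 6) | Effective n per arm | Actual two-sided error |
|---|---|---|---|
| 0.1 | 1.4–1.5 | 143–133 | 10–11% |
| 0.3 | 2.2–2.5 | 91–80 | 19–22% |
| 0.5 | 3.0–3.5 | 67–57 | 26–30% |

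Example, m = 6 and ICC 0.3: DE = 1 + 5 × 0.3 = 2.5; 200/2.5 = 80; 1.96/√2.5 = 1.24; error 21.5%. Simulating an individual-level t-test (20,000 runs, 34 households of 6 or 40 of 5 per arm) gives rates within about one percentage point of the formula.

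With four enrolled per household, DE is 1.3, 1.9 and 2.5, and effective n is 154, 105 and 80.

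**5. What this does to power.** Multiplying n by four corresponds to halving the effect, to 0.39 μg/g. At that effect, about 101 independent people per arm give 80% power, and 200 give 96.8%. With m = 5 to 6, before dropout:

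| Assumed ICC | Power at 0.39 μg/g |
|---|---|
| 0.1 | 90–89% |
| 0.2 | 83–80% |
| 0.3 | 76–71% |
| 0.5 | 65–59% |

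At the full cited effect of 0.78 μg/g, power is 93–89% even at ICC = 1. At a quarter of it (0.195 μg/g), power is 54% without clustering and 37–34% at ICC 0.2.

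**The case against.** A reader might infer that every arm comparison in the plan has an inflated false-positive rate. The article does not support that, because it prints no arm comparison. Its correlations and regressions relate a person's own urinary or hair arsenic to outcomes. That exposure varies within a household, so the design effect for a fully shared treatment does not carry over to them directly. A fuller protocol or SAP may already adjust for household. The error rates above therefore hold only if the arms are compared on individuals without adjustment, and only under the assumed ICCs.

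A reader might also infer that a stated power is false. It is not: the 0.80 belongs to 26 per group, the article itself says that 26 is too few, and no power is claimed for 200. The roughly eightfold increase also absorbs a good deal of clustering, as step 5 shows.

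Finally, the two household counts are not a firm contradiction. The 34 is a conditional illustration, the 80 is approximate, and both fit the stated range of four to eight members.

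All of this stands as a limit on the point. It does not remove it. The Sample size section lists its reasons for inflation and leaves clustering out, so the margin was reserved for other purposes. The Data analysis section goes as far as a p-value screen and a 5% change rule for confounders but has no household term, and outcomes in its regressions can still be correlated within households.

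**Conclusion.** The design is clustered by household, and the printed sample size and analysis methods do not reflect that. Under assumed ICCs of 0.1 to 0.5 and 5 to 6 enrolled per household, 200 per arm is worth between about 143 and 57 independent people; the loss is smaller if fewer members aged 14 and over enrol. An unadjusted comparison of individuals would have a type I error of about 10% to 30% instead of 5%.

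The trial is not shown to be too small. At half the cited effect, power stays near or above 80% up to an ICC of about 0.2 before dropout, and it falls below that only at higher ICCs or smaller effects. The need for household-level analysis does not depend on the effect size: any positive ICC inflates the error of an unadjusted comparison, and a larger n does not correct it. The household count is a minor matter of wording.

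**What to change.** - Keep 400 participants.
- State that the arms will be compared with a mixed model with a random household intercept, or with household-clustered standard errors and small-sample degrees of freedom based on the 68 to 80 households. A Bari effect is optional, since households in one Bari may be in different arms.
- Account for household in the planned regressions of outcomes on arsenic as well.
- Restate the sample size justification with a design effect 1 + (m − 1) × ICC over a stated ICC range such as 0.1 to 0.5, with m the enrolled members aged 14 and over per household, and say which effect 200 per arm is meant to detect.
- As a minor point, give one household count based on enrolled members. Thirty-four households per group would yield 34 × 5 = 170 people if five enrol in each, and 34 × 4 = 136 if four do.

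The cost is a change of wording in the sample size and analysis sections. Household is already coded in the participant numbers, so no new data and no extra participants are needed. Intervals will be wider than an unadjusted analysis would show.
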